### Inclusion criteria for CLBP subjects

Adults aged between 18 and 59 years [45].Patient suffering from low back pain for at least 3 months and referred by an orthopedic doctor or general physician.Participants with enough physical autonomy to take part in physical activities such as performing lumbar endurance and lumbar positioning test required of the study.

### Exclusion criteria CLBP subjects

Low back pain patients with neurological deficit, any neurological disorder, post spinal fractures, history of spinal tumors, cauda equina syndrome, tuberculosis spine, any congenital spine anomalies, vestibular issue, joint instability in lower limb, cardiorespiratory problem, and hip arthritis.Patient under antidepressive medication and antihypertensive medicationPatient unwilling to participate

### Inclusion criteria for asymptomatic subjects

Adults aged between 18 and 59 years.Either gender.

### Exclusion criteria for asymptomatic subjects

History of (H/o) previous lower back injury.Participants with congenital spine anomalies, vestibular issue, joint instability in lower limb, cardiorespiratory problem, and hip arthritis.H/o inflammatory, infectious disease, and malignancy in the spinePatient under antidepressive medication and antihypertensive medication

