Kinesiophobia is described as an excessive, unreasonable, and crippling fear of performing a physical motion due to a feeling of vulnerability to a painful injury or reinjury [19]. Clinical studies suggest that an exaggerated negative cognitive response toward actual pain known as pain catastrophizing and fear of movement/(re)injury (kinesiophobia) is important in the etiology of chronic low back pain and associated disability [20]. These findings are consistent with a cognitive-behavioral perspective that underscores the importance of maladaptive interpretations of bodily sensations [20].

The mechanism can be described as follows: persons who catastrophically misinterpret innocuous bodily sensations, including pain, are likely to become fearful of pain, which results in at least two processes. First, pain-related fear is associated with avoidance behaviors and the avoidance of movement and physical activity in particular. Avoidance also means withdrawal from rewarding activities such as work, leisure, and family. Second, pain-related fear is associated with increased bodily awareness and pain hypervigilance. Hypervigilance, depression, and disuse are known to be associated with increased pain levels and hence might exacerbate the painful experience. This model is used to develop successful treatments [20–22].

Thus, kinesiophobia is correlated to pain-related interference and triggers motor activity changes that influence activities related to pain and pain-related disability management and control [18]. The prevalence of kinesiophobia in chronic pain varies from 50 to 70% [23]. A higher degree of kinesiophobia is correlated with higher levels of perceived pain [24] and lower level re-entry into pre-injury activities for all [CMP] chronic musculoskeletal pain conditions [25]. Thus, clinicians should consider kinesiophobia as an important factor in their preliminary assessment of patients with chronic LBP [18].

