### Sample size

As for the calculation of the sample size, the odds ratio taken is 2 with the prevalence of 70% kinesiophobia [17] among CLBP patients and assumed the prevalence of 10% kinesiophobia among the controls, with the minimum required sample size of 600 [200 cases + 400 controls]. The case-control ratio taken is 1:2. The controls will be invited participants/patients who have no complaints of lower back pain at the Thumbay Physical Therapy & Rehabilitation Hospital, Ajman. All possible confounding factors will be controlled through subgroup analysis in later part during data analysis. The patients and controls will be identified from the outpatient clinic prospectively.

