#### Kinesiophobia

Fear of movement/injury or reinjury will be assessed using the Tampa Scale for Kinesiophobia (TSK), a scale with 17 self-reporting items with scores ranging from 17 (absence of fear) to 68 (highest fear) [46]. Tampa Scale for Kinesiophobia has been reported to have good reliability in patients with CLBP [47].

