### Statistical analysis

The statistical analysis will be computed using SPSS Statistics software, version 27 (IBM, Chicago, IL, USA). The data analyses will be conducted by a statistician. Continuous variables will be summarized using standard measures of central tendency and dispersion, either as mean and standard error, or median and interquartile range. Dichotomous or categorical variables will be summarized by frequencies or denominators and percentage.

Kinesiophobia, lumbar endurance, and joint position sense will be compared between patients and controls using appropriate statistical tools. Kinesiophobia scores will be correlated with lumbar extensor endurance and proprioception joint position errors, pain intensity, and functional ability. Chi-square test will be used to find the association between kinesiophobia and lumbar endurance and joint position sense. Spearman rank correlation will be used to find the correlation between kinesiophobia, pain, and functional ability. Simple and multiple binary logistic regression will be used to determine crude and adjusted odds ratio for kinesiophobia, lumbar position sense and kinesiophobia, and lumbar endurance.

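### Previous lower back injury excludes controls but not cases, so the groups are restricted unequally on a plausible correlate of kinesiophobia and the patient-control contrast may be biased

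*Protocol article*

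**What the plan says.** The protocol article (Methods, Exclusion criteria for asymptomatic subjects) removes any control with "History of (H/o) previous lower back injury". The corresponding list for patients (Exclusion criteria CLBP subjects) begins "Low back pain patients with neurological deficit, any neurological disorder, post spinal fractures, history of spinal tumors" and continues with other diagnoses. Spinal fracture is its only injury-type item, so a patient with an earlier strain, sprain or other back trauma remains eligible.

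Control status is already established elsewhere. The Sample size section states "The controls will be invited participants/patients who have no complaints of lower back pain". The Background describes kinesiophobia as "fear of performing a physical motion due to a feeling of vulnerability to a painful injury or reinjury", and the Kinesiophobia section under Outcome measures describes what the Tampa Scale measures in similar terms. The Statistical analysis section then says "Kinesiophobia, lumbar endurance, and joint position sense will be compared between patients and controls", and it adds crude and adjusted odds ratios from logistic regression.

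The article does not explain the unequal criterion. Past back injury is not among the items collected under Procedures, nor among the lifestyle factors listed with the PECO model.

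**The concern.** In a case-control study, controls should represent the population from which the cases arise. A pain-free person with an old, healed back injury belongs to that population: such a person can develop chronic low back pain and would then be accepted as a case. Here that person is barred as a control but admitted as a case.

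This matters because of the exposure under study. Reinjury presupposes an earlier injury, so on the article's own definition past injury is a plausible source of kinesiophobia. If it is one, the exclusion lowers kinesiophobia among controls and leaves it unchanged among cases, and the contrast between the groups is too large. Endurance and position sense would be affected in the same way only if an old injury leaves a deficit in people who are now pain-free. The article is silent on that.

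The primary aim is a comparison with asymptomatic individuals, so the unequal criterion bears on a main result.

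**Working it through.** **1. The two lists side by side.** Congenital spine anomalies, vestibular problems, lower-limb joint instability, cardiorespiratory problems, hip arthritis and the two medication classes appear on both lists. The lists are therefore largely parallel. Previous lower back injury is on the control list only, and spinal fracture is named on the case list only.

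**2. The plan's own figures.** The Sample size section gives an odds ratio of 2, 10% kinesiophobia among controls, a 1:2 ratio, and 200 cases plus 400 controls. The implied prevalence in cases is

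2 × 0.10 / (0.90 + 2 × 0.10) = 0.1818.

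Alpha and power are not stated. With an assumed two-sided 0.05 and 80% power, the standard two-proportion formula gives 205 cases + 410 controls = 615, and the pooled-variance version gives 196 cases. Power at 200/400 is 79.1%. The stated 600 is therefore reproduced closely from an odds ratio of 2 and 10% in controls. The exclusion does not alter this arithmetic. It affects what the control prevalence, and the odds ratio built on it, represent.

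**3. Effect of the exclusion on the odds ratio.**

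Inputs:
- k = 0.10, kinesiophobia in never-injured controls. The article assumes 10% among controls, and its enrolled controls are never-injured.
- q, the share of otherwise eligible pain-free people with a past back injury. Not in the document; assumed 10%, 20% or 30%.
- R, the odds ratio linking past injury to kinesiophobia in pain-free people. Not in the document; assumed 1 (no link), 1.5, 2 or 3.

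Formulas:
- Odds in the injured = R × k/(1 − k) = R × 0.1111. Their prevalence k_i is 14.3%, 18.2% or 25.0% for R = 1.5, 2 or 3.
- Prevalence had they been admitted: k_t = q × k_i + (1 − q) × k.
- Inflation factor = [k_t/(1 − k_t)] / [k/(1 − k)]. The odds in cases cancel, so no case prevalence is needed.

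Two cells worked through:
- q = 10%, R = 1.5: k_t = 0.1 × 0.143 + 0.9 × 0.10 = 0.1043; factor = 0.1164/0.1111 = 1.048.
- q = 30%, R = 3: k_t = 0.3 × 0.25 + 0.7 × 0.10 = 0.145; factor = 0.1696/0.1111 = 1.526.

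| Injured share q | R = 1 | R = 1.5 | R = 2 | R = 3 |
|---|---|---|---|---|
| 10% | 1.00 | 1.048 | 1.092 | 1.169 |
| 20% | 1.00 | 1.096 | 1.185 | 1.345 |
| 30% | 1.00 | 1.145 | 1.280 | 1.526 |

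The factor compares the planned crude odds ratio with the one obtained if previously injured pain-free controls were admitted. An observed odds ratio of 2 would correspond to 2/1.048 = 1.91 at the low end, 2/1.185 = 1.69 for q = 20% and R = 2, and 2/1.526 = 1.31 at the high end. If past injury were linked to less fear (R = 0.8, q = 20%), the factor would be 0.96 and the contrast slightly understated.

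**4. Can the analysis repair it?** Adjusting for injury history cannot, because every control has the same value and there is no overlap. Restricting the cases to those without previous injury makes the two sides alike, but this needs injury history to be recorded in cases.

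**The case against.** The other side has five reasonable arguments.

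- The comparator is asymptomatic people, and a strictly back-healthy reference group is a defensible choice.
- The injury line may simply be a broader wording of the fracture line on the case list.
- The definition covers fear of injury as well as reinjury, so past injury is not necessary for kinesiophobia, and the article gives no data linking the two.
- Confounders are to be handled by subgroup analysis, which could include restriction.
- A condensed article may leave the recording of injury history to the case form.

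Some of this stands. Direction and size are not established by the document. Past injury is a correlate of the exposure, not the exposure itself. Restricting the cases is a workable analysis.

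The rest does not dispose of the point. Freedom from back pain complaints already defines a control, so the injury line goes further than that purpose needs. If a back-healthy reference group is intended, the article should say so. A wording slip would still need reconciling, because as written the criterion covers far more than fractures. Subgroup analysis can help only if cases are asked the question.

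A reader might go further and infer a much larger bias by treating 10% as the prevalence before the exclusion and giving the injured 20-30% kinesiophobia. Control prevalence then falls to between 8.9% and 5.0%, and a true odds ratio of 2 reads 2.3 to 4.2. The document does not support this. Its 10% refers to the study's controls. The upper figure needs an injury-kinesiophobia odds ratio of (0.30/0.70)/(0.05/0.95) = 8.1. Scaling up the odds ratio of 21 implied by 70% versus 10% is no better, since that figure conflicts with the article's own odds ratio of 2, which is a separate problem.

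**Conclusion.** The unequal restriction is certain from the text and is unexplained. That it biases the kinesiophobia contrast away from the null is plausible from the article's own definition, but depends on past injury raising kinesiophobia in pain-free people. Under the stated assumptions (10% in never-injured controls, 10-30% previously injured, link of 1.5 to 3) the case-control odds ratio is inflated by about 5-53%, and by nothing if there is no link. Against a design odds ratio of 2, the middle of that range is large enough to matter for interpretation.

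The point covers the patient-control comparisons only. The planned correlations of kinesiophobia with pain, function, endurance and position sense within CLBP patients are unaffected. A reader might also infer that the contrast is certainly inflated, or that no later analysis can mend it. Neither follows: the direction is conditional, and restricting the cases is an available remedy.

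**What to change.** Reconcile the two exclusion lists so that the back-injury criterion applies alike to cases and controls. One way is to admit pain-free controls with a healed injury, record injury history in everyone and adjust for it.

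If the control criterion is kept, state why and ask cases the same injury-history question. Word it as injury before the current episode, so that an injury that started the present pain is not counted. Then add a sensitivity analysis of the patient-control comparisons of kinesiophobia, endurance and position sense, limited to cases without previous injury. Keep the all-cases analysis as planned: making never-injured cases the main comparison would change the target population from the CLBP patients defined in the inclusion criteria.

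The cost is one form item, one extra analysis, and lower precision in the restricted comparison, since an unknown share of the 200 cases would drop out of it.

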### Procedures

The initial screening of participants will be performed by a physiotherapist (examiner 1) during the first physical therapy appointment. Then, the participants will be instructed to fill a Tampa Scale for kinesiophobia which is a questionnaire consisting of socio-demographic information (age, gender, weight, height), pain characteristics (pain area and associated symptoms); fear-avoidance behavior and physical examination carried out by the examiner. The evaluation of pain intensity and function will be performed through self-reported questionnaires (visual analog scale—VAS and Patient-specific Functional Scale). The physiotherapist (examiner 2) who carries out the lumbar endurance and position sense will be blinded for the cases and control group.

### Outcome measures

Three levels of specifications in reporting five outcome measures to be used in this study are provided in Fig. 1a, b.

**Fig. 1 Fig1:**
[figure not shown]
**a**, **b** Level of specification in reporting outcome

#### Kinesiophobia

Fear of movement/injury or reinjury will be assessed using the Tampa Scale for Kinesiophobia (TSK), a scale with 17 self-reporting items with scores ranging from 17 (absence of fear) to 68 (highest fear) [46]. Tampa Scale for Kinesiophobia has been reported to have good reliability in patients with CLBP [47].

#### Lumbar extensor endurance

All these experiments will be conducted in a laboratory setting. The subjects will be tested during a 1-h session and will be asked to undergo a body weight-dependent isometric back extension (Sorensen) test on a horizontal table [48]. Sorensen test will be performed in the prone position, with the iliac crests aligned with the table edge and the lower limbs fixed by straps at the ankles and below the knees. During the test, the participants will be instructed to keep their body (head, arms, and trunk) unsupported, horizontal to the ground, as long as they could, with their arms crossed at the chest [48]. To maintain the horizontal position throughout the test, the investigator will give them verbal feedback, and the test will be ended when they could not hold the test position. Verbalized encouragement will be provided throughout the test. The participants will be instructed to maintain the lumbar lordosis position as stable as possible. The endurance will be recorded by investigator with the help of a stopwatch in seconds. A chair with cushioned seat (or with a pillow over the seat) will be placed in front of the subject so that he can support himself if fatigued during the test. The stopwatch will be stopped as soon as the subject gets fatigued or can no longer sustain the position [48].

#### Lumbar repositioning tests

Subjects will be instructed not to perform any strenuous physical activity for 24 h prior to testing and to not drink or eat 2 h prior to testing (to minimize cutaneous input from a distended abdomen). For testing, subjects will be blindfolded to eliminate visual input and the room will be kept quiet to limit auditory input. Subjects will be asked to stand in a neutral position, with their knees straight and weight equally on both feet. The primary sensor digital inclinometer will be placed over the lateral chest (T12 level) and secondary sensor over the hemi-pelvis (S1 level) in the sagittal plane to measure lumbar reposition errors in flexion. A primary sensor (T12) and secondary sensor (sacral midpoint) in the frontal plane will be used to record lateral bending angle error. Velcro straps will be used to secure the digital inclinometer for testing. Dualer IQ digital inclinometers (DIs; J-Tech Medical, Midvale, UT, USA) will be used to measure lumbar joint position error. Digital inclinometers are reliable, fast, and high in measurement precision and allow clinicians to evaluate ROM and proprioception using dynamic inclinometry like that used in other goniometric protocols [49]. The digital inclinometers have shown test-retest reliability for measuring spinal ROM, and evaluation protocols are well established and endorsed by the American Medical Association (AMA) [49].

For neutral lumbar positioning (NLP) testing, subjects will be asked to maintain the lumbar spine in a neutral position with their eyes closed. The inclinometer will be calibrated to a starting position (0 degrees) by the examiner [49]. The subjects will be asked to memorize this neutral position for few seconds, perform active full flexion, and then relocate to neutral position. Subjects will be instructed to perform the test as accurately as possible and indicate verbally when they thought they had returned to the starting position. Relocation accuracy will be measured in degrees. The NLP test will be performed in one direction only (lumbar flexion) [49].

For target lumbar positioning (TLP), the examiner guided in a slow steady pace that subject’s lumbar spine reached to a predetermined target, 50% of the maximum ROM. This range will be chosen so that all subjects could achieve it. The spine will be maintained in the target position for 5 s, subjects will be asked to remember the position, and the lumbar spine will be guided to a neutral position [49]. Subjects will then be asked to actively reposition by bending the spine to the target position. When the subjects reach the reference position, relocation accuracy will be measured in degrees [49]. Subjects will perform a total of three trials for each movement direction (flexion, lateral bending). The average of three trials will be used for analysis. The order in which movement directions will be tested will be randomized using a simple lottery method. Only the absolute error will be taken as a measurement; absolute error is the difference between the actual angles relative to the target angle and thus has no directional bias when compared to constant error or relative error.

#### Pain

Pain will be measured using a visual analog scale (VAS). The visual analog scale consists of a 10-cm line, with the left extremity representing (absence of pain) and the right extremity indicating (great pain) [50]. As per the recent evidence, either VAS or NRS scores are the validated predictors of the disability in CLBP conditions [51]. Participants were asked to indicate in the scale their current level of pain, higher values being related to more intense pain [52].

#### Functional ability

Functional ability will be measured using Patient-specific Functional Scale [PSFS] where patients are asked to identify up to five important activities they are unable to perform or are having difficulty with as a result of their problem, e.g., putting socks on, shopping. Patients are asked to rate (on an 11-point scale) the current level of difficulty associated with each activity, where “0” represents “unable to perform” and “10” represents “able to perform at prior level.” Patients select a value that best describes their current level of ability on each activity assessed [53]. The PSFS can be used with confidence for measuring change over time in individual patients within a limited range of musculoskeletal conditions, including knee, low back, or neck dysfunction [54].

The PECO model is provided for the reader below for comprehensive understanding of this study.

### PECO model for this study

P—Patient with chronic lower back painE—Primarily kinesiophobia and other confounding factorsC—Asymptomatic subjectsO—Lumbar position sense, lumbar muscle endurance, pain, and functional ability

Lifestyle factors, such as excess weight, physical inactivity, poor diet, and smoking, are linked to low back pain chronicity and disability. Smoking was categorized as non-smoker, often inhale secondhand smoke, quit smoking in less than 1 year, and smoker. Alcohol consumption was divided as not drinking, ≤ 1 glass/week, 2–3 glasses/week, and ≥ 4 glasses/week. Physical activity including any form of physical exercise was categorized as none, ≤ 2 h/week, 3–6 h/week, and ≥ 7 h/week. Dietary habits were categorized into 3 groups: (1) intake of no or low vegetables with high meat, (2) intake of moderate vegetables with moderate meat, and (3) intake of high vegetables with no or low meat [55, 56].

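### The smoking levels overlap and pool long-term ex-smokers with never-smokers, and the activity and alcohol bands are gap-free only in whole units, so assignment is ambiguous

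*Protocol article*

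**What the plan says.** Under the PECO heading in Methods, the exposure line covers kinesiophobia together with further confounders. The paragraph that follows opens: "Lifestyle factors, such as excess weight, physical inactivity, poor diet, and smoking, are linked to low back pain chronicity and disability". It then fixes the categories:

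- Smoking: "Smoking was categorized as non-smoker, often inhale secondhand smoke, quit smoking in less than 1 year, and smoker".
- Alcohol: "Alcohol consumption was divided as not drinking, ≤ 1 glass/week, 2–3 glasses/week, and ≥ 4 glasses/week".
- Activity: "Physical activity including any form of physical exercise was categorized as none, ≤ 2 h/week, 3–6 h/week, and ≥ 7 h/week".
- Diet: "Dietary habits were categorized into 3 groups: (1) intake of no or low vegetables with high meat", followed by a moderate/moderate group and a high-vegetable, low-meat group.

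No rounding rule is given, and no rule for a person who fits two categories or none. Two references are cited for the categories.

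Three other places bear on how such items would be used. The Sample size section says: "All possible confounding factors will be controlled through subgroup analysis in later part during data analysis". The Statistical analysis section plans crude and adjusted odds ratios from simple and multiple logistic regression. The third aim, at the end of Background, is to estimate how various factors are associated with chronic low back pain, endurance and position sense.

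**The concern.** A categorical covariate works only if each participant belongs to exactly one level. If two levels can both be right, the choice depends on how the question is read. If a level is missing, unlike people are put together.

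Two uses of the data are at stake. First, if lifestyle factors are adjusted for or used to form subgroups, a poorly measured factor is only partly controlled, and some confounding stays in the adjusted odds ratio. Activity is the item to watch: it could plausibly go with both less fear of movement and a longer Sorensen hold. Second, if smoking is among the factors of the third aim, a reference group that mixes never-smokers with people who smoked for years and stopped would blur its association.

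The smoking fault cannot be repaired at analysis. Past smoking that was never recorded cannot be recovered from the four levels.

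**Working it through.** There is no plan figure to reproduce. The check is whether each possible answer meets exactly one printed category. All inputs are the limits in the PECO section.

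**Smoking.**

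| Person | Levels met as printed |
|---|---|
| Never smoked, little exposure | non-smoker |
| Never smoked, often exposed to others' smoke | non-smoker and secondhand |
| Current smoker, often exposed | smoker and secondhand |
| Quit under 1 year ago | quit under 1 year (also secondhand, if often exposed) |
| Quit 1 year ago or more | no level of their own; non-smoker by default |

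Rounding cannot remove the overlap, because the variable mixes two questions: the person's own smoking history and exposure to other people's smoke. The last row is a loss of information. The scheme separates recent quitters, so it treats past smoking as relevant, and then has nowhere to record it once a year has passed.

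**Activity (h/week).** The bands are none, ≤ 2, 3–6 and ≥ 7.

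- 2 meets ≤ 2; 3 and 6 meet 3–6; 7 meets ≥ 7.
- 2.5 and 6.5 meet no band. The uncovered intervals are above 2 to below 3, and above 6 to below 7.
- 0 meets both none and ≤ 2 if read literally. This disappears if the explicit zero category takes precedence.

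**Alcohol (glasses/week).** The bands are not drinking, ≤ 1, 2–3 and ≥ 4.

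- 1.5 and 3.5 meet no band.
- 0 meets two, with the same simple resolution.

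In whole hours and whole glasses, every value from 0 upward has a band. The numeric gaps therefore depend on how answers are recorded. Hours of exercise readily give fractions: five half-hour sessions make 5 × 0.5 = 2.5 h.

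**Diet (side observation).** The three groups pair low vegetables with high meat, moderate with moderate, and high vegetables with low meat. A participant high on both or low on both has no group.

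**Link to the analysis.** The Sample size section promises control of confounding without naming a variable, and the Statistical analysis section promises adjusted odds ratios without naming a covariate. The link to the lifestyle items is that their list stands directly under the PECO line that mentions other confounders. No other purpose for collecting them is stated. That is a reasonable inference, not a stated plan.

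**The case against.** The strongest reply is that this is loose labelling in a condensed article. Tie-break and rounding rules belong on the data form, and the cited sources may supply them. Bands written in whole numbers are normally meant for whole-number answers, and then nothing is missing. A long-term ex-smoker does have a place, as a current non-smoker. A smoker exposed to others' smoke would naturally be coded as a smoker if the levels are read as a ranking of exposure.

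Much of this stands. The activity and alcohol gaps close in whole units, and a ranking rule would settle the smoker's case. What remains is that no ranking is stated, that secondhand exposure and personal smoking share one variable, and that a printed scheme with no level for earlier quitters is badly fixed as it stands. A form that followed it faithfully would carry the same fault.

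Four stronger readings are tempting and are not supported:

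- *That participants are misclassified.* The text leaves assignment undefined; it does not show wrong assignment.
- *That the study undertakes to control all confounders with these variables.* No section names them as covariates or subgroup factors, and the third aim does not name smoking.
- *That the four physiotherapists would code differently.* The Discussion gives them the screening and says they will all receive protocol information to keep data collection uniform. Nothing says they assign lifestyle categories.
- *That a head count measures the problem.* If 10% to 20% were long-term ex-smokers, that would be 0.10 × 600 = 60 to 0.20 × 600 = 120 people. If 10% to 15% gave activity answers in the gaps, it would be 60 to 0.15 × 600 = 90. These shares are pure assumptions, the ex-smokers would still have a default level, and a count is not a bias.

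**Conclusion.** The point holds as a minor one. The smoking variable has overlapping levels and cannot separate people who quit a year or more ago from never-smokers; both faults can be read directly from the printed list. The activity and alcohol bands are sound for whole-unit answers and incomplete otherwise.

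The consequence is conditional. If these items serve as the other confounders of the PECO list, some participants may be misclassified, confounder control would be weaker than the article suggests, and any smoking association under the third aim would be blurred. The size cannot be computed, since the article gives no distribution of smoking, activity or alcohol and no strength for their links with kinesiophobia or the outcomes. For the main odds ratio the effect is probably small; that is a judgement, not a result. Nothing here shows that the main result would be biased to a degree that matters.

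**What to change.** Replace the smoking item with four exclusive levels: never; quit 1 year ago or more; quit under 1 year ago; current. Ask about frequent secondhand smoke as a separate yes/no question.

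Record activity in hours per week and alcohol in glasses per week as numbers. If bands are preferred, make them contiguous; for activity: 0; above 0 to under 3; 3 to under 7; 7 or more. Recording numbers does not force a linear term in the model, because bands can still be formed afterwards. Vegetable and meat intake could be asked as two separate items in the same edit. It would also help to state which of these variables enter the adjusted models or subgroups.

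The cost is a small change to the data form and little extra burden for participants. Timing matters more. Methods gives recruitment as May to November 2022, the Discussion expects a start on 25 May 2022, and the article appeared on 6 June 2022, so enrolment may already have begun. The change should be made as early as possible. Anyone already enrolled would need the smoking item asked again, or would have to be coded as unknown for it.
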